### Outcomes {12}

The primary outcome of this investigation is to determine the prevalence of successfully erupted maxillary permanent central incisors at 6 months following removal of the supernumerary tooth (obstruction). As per previous prospective investigations of unerupted teeth, the primary endpoint of the study is defined as the eruption (successful outcome) of the unerupted maxillary central through the gingival mucosa during the 6-month observation period [23]. Clinically, the amount of clinical crown visible should *allow* the placement of an orthodontic attachment or removal of the bonded gold chain attachment and placement of an orthodontic attachment/bracket. Secondary outcome measures will include (1) the effect of initial tooth position (assessed radiographically) on the time taken for the tooth to erupt, (2) time taken to align the unerupted tooth to the correct occlusal position, (3) gingival aesthetics associated with the erupted central incisor and (4) changes in the self-reported Oral Health Related-Quality of Life (OHRQoL) (pre- and post-treatment).

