### Data collection and management

#### Plans for assessment and collection of outcomes {18a}

Data will be collected at five time points: (T0) pre-treatment (baseline) records: dental study casts, extra- and intra-oral photographs, radiographs, completion of the Quality of Life Questionnaire and patient and participant demographics; (T1) prior to randomisation to either surgical removal of the supernumerary tooth, gold chain bonding and immediate post-surgical orthodontic traction (group 1) or surgical removal of the supernumerary tooth and monitoring eruption of the unerupted incisor for a period of 6 months (group 2): intra-oral photographs; (T2) following eruption of the incisal edge of the unerupted maxillary central incisor through the gingival mucosa: dental study casts and extra- and intra-oral photographs; (T3) unerupted maxillary central incisor aligned to correct occlusal level compared to contra-lateral maxillary central incisor: dental study casts, extra- and intra-oral photographs and completion of the Oral Health-Related Quality of Life Questionnaire; and (T4) 3 months post-treatment: dental study casts, extra- and intra-oral photographs and completion of the Oral Health-Related Quality of Life Questionnaire.

The Oral Health-Related Quality of Life Questionnaire (8–10 years old) to be used in this trial is a previously validated instrument which has been used reliably in the UK population [24, 25]. In either intervention group, if after the observation period of 6 months following removal of the supernumerary tooth the central incisor has failed to erupt, the following records will be taken: intra-oral photographs, study models and radiographs.

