## Statistical methods

### Statistical methods for primary and secondary outcomes {20a}

The primary outcome of the trial is the successful eruption (yes/no) of the impacted maxillary incisor, which is ascertained clinically in an objective matter and is clinically relevant (binary outcome). Secondary outcomes planned include (i) time taken for the maxillary incisor to erupt clinically after surgical removal of the supernumerary (continuous outcome in days), (ii) gingival aesthetics outcome according to Parkin et al. [26] (continuous outcome on a 100-cm visual analogue scale [VAS]) and (iii) patient-related outcomes included in the Oral Health-Related Quality of Life Questionnaire [24] (continuous scale outcome with total score and sub-scores for each category). Possible risk factors that are planned a priori to be investigated include patient age, patient sex, patient ethnicity, impacted incisor’s maturity, impacted incisor’s position (height, inclination and orientation; as described in the trial’s protocol) and the supernumeraries’ number or morphology (conical, premolariform, incisiform, complex odontoma, etc.). The initial crude differences between the groups will be assessed with the chi-square test for the primary outcome or the t-test for independent samples for the secondary outcomes (or non-parametric equivalents). The crude effect of intervention groups on the primary/secondary outcomes (with patient as the unit of analysis) will be further assessed with generalised linear models (after appropriate model diagnostics) with relative risk (RR) for the primary outcome or unstandardised regression coefficient for the secondary outcomes and their corresponding 95% confidence interval (CI). Furthermore, regression models will be adjusted for the potential impact of any of the above-listed confounders, by adding one covariate at a time in the simple model and retained if the change-in-estimate is at least 10% [27]. All analyses will be done per protocol by the statistician in a blind manner using a coded dataset in Stata 14.2 (StataCorp., College Station, TX, USA) with a significance level set at a two-sided P-value of 0.05 for all analyses.

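### The quality-of-life score is collected at T0, but no planned model uses it as a covariate, so precision is lost that prespecified baseline adjustment would recover at no cost

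*Protocol article*

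**What the plan says.** **Outcome.** The protocol article, Outcomes {12}, lists as its fourth secondary outcome "4) changes in the self-reported Oral Health Related-Quality of Life (OHRQoL) (pre- and post-treatment".

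**Collection.** Under Plans for assessment and collection of outcomes {18a}, the T0 records include "completion of the Quality of Life Questionnaire and patient and participant demographics". The questionnaire appears again at T3, defined as "T3) unerupted maxillary central incisor aligned to correct occlusal level compared to contra-lateral maxillary central incisor", and at T4, three months post-treatment. The records listed for T1, for T2 (eruption) and for non-eruption at 6 months do not include it.

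**Analysis.** Statistical methods {20a} lists the quality-of-life variable as "patient-related outcomes included in the Oral Health-Related Quality of Life Questionnaire [24] (continuous scale outcome with total score and sub-scores for each category"). It does not say whether the value compared is a change score or a post-treatment score. The steps are:

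1. An initial crude comparison by "the t-test for independent samples for the secondary outcomes (or non-parametric equivalents").
2. A generalised linear model giving an "unstandardised regression coefficient for the secondary outcomes and their corresponding 95% confidence interval (CI").
3. Adjusted models. The candidate covariates begin "Possible risk factors that are planned a priori to be investigated include patient age, patient sex, patient ethnicity" and go on to incisor maturity, incisor position, and supernumerary number or morphology. Each is added singly and kept only if the estimate changes by at least 10%.

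The section on additional analyses {20b} plans nothing beyond these adjusted models.

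**The concern.** For a repeatedly measured score, the child's own baseline value is usually among the strongest predictors of the later value. Here it is collected before treatment, yet it is not on the covariate list for any step.

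The selection rule compounds this. Change-in-estimate selection is built to find confounders. In a randomised comparison a baseline score is expected to be balanced, so its main benefit is a smaller standard error, not a shifted estimate. A rule that looks only at the shift can reject the covariate that helps most.

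What is at stake is the chance of seeing a quality-of-life difference in a trial of 92 children that was sized for a binary eruption outcome. A wide interval here could be read as no difference.

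**Working it through.** The plan gives no figure for quality of life, so there is nothing to reproduce. Its 40 evaluable children per group (Sample size {14}) is used below only as a group size, and the number with a T3 score may be lower.

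**Inputs**
- n = 40 per group, two-sided 5% level, 80% power: from the article.
- ρ, the correlation between the T0 and post-treatment score: not in the article. Assumed, and shown from 0.3 to 0.8.
- Equal standard deviation (SD) at T0 and follow-up, and a common linear slope in both groups: assumed.

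**Formulas** (variance relative to a post-treatment score)
- Post score: 1
- Change score: 2(1 − ρ)
- Linear model with T0 as covariate: 1 − ρ²
- Adjusted against change: (1 − ρ²) / [2(1 − ρ)] = (1 + ρ)/2, a saving of (1 − ρ)/2
- Adjusted against post: 1 − ρ², a saving of ρ²
- Detectable difference: (1.96 + 0.84) × √(2/40) × √(relative variance) = 0.63 SD × √(relative variance)

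| Assumed ρ | Variance, adjusted/change | Variance, adjusted/post | Detectable, change score (SD) | Detectable, adjusted (SD) |
|---|---|---|---|---|
| 0.3 | 0.65 | 0.91 | 0.74 | 0.60 |
| 0.5 | 0.75 | 0.75 | 0.63 | 0.54 |
| 0.6 | 0.80 | 0.64 | 0.56 | 0.50 |
| 0.7 | 0.85 | 0.51 | 0.49 | 0.45 |
| 0.8 | 0.90 | 0.36 | 0.40 | 0.38 |

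The post-score comparison detects 0.63 SD at every ρ. For an assumed true difference of 0.5 SD at ρ = 0.5, power is 61% with either unadjusted score and 73% with T0 as a covariate.

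**The 10% rule.** Let D be the chance difference in mean T0 score between groups, in SD units. Adding T0 to a post-score comparison moves the estimate by ρD. With ρ = 0.5 and an unadjusted estimate of 0.5 SD, the rule keeps T0 only if 0.5 × |D| ≥ 0.10 × 0.5, that is, if |D| ≥ 0.10 SD. Under randomisation D has mean zero and standard error √(2/40) = 0.22 SD. Retention therefore depends on the imbalance that happens to arise, although adjustment would cut the variance by 25% in expectation.

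**Timing.** Set side by side, the schedule and the outcome definition give a pre/post-treatment comparison whose post-treatment points are triggered by alignment. No questionnaire is scheduled between T0 and alignment. The arms may therefore be scored at different times since surgery, and a child whose tooth is not aligned has no T3 score.

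**The case against.** **The t-test is only the first step.** A reader might infer that quality of life is compared by an unadjusted t-test alone. The article does not support that: it labels the t-test as crude and follows it with regression and adjusted models. The accurate criticism is that none of these has the T0 score as a covariate.

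**A change score already uses T0.** This stands. The Outcomes section speaks of changes, and if change is analysed the only loss is the step from change score to baseline adjustment: 25% of variance at ρ = 0.5 and 10% at ρ = 0.8. The larger post-score figures apply only if post-treatment scores are compared, which the analysis section leaves open. Either unadjusted comparison is unbiased for complete randomised groups, so this is about efficiency.

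**Model detail may sit in a fuller document.** Partly fair. The covariates are one shared list for all outcomes, and a fuller protocol or SAP may treat the baseline score separately. But the article itself fixes the list and the retention rule and plans no further analyses, so the gap is in what is stated.

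**The stated question is pre- versus post-treatment.** This stands too. A reader might infer that the test misses the waiting period, or that a six-month score should become the main comparison. The wait is missed because of the visit schedule, which baseline adjustment would not change. Replacing the main comparison would change the sponsor's question.

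**Planning rates are not missing-data rates.** The planning values imply 1 − 0.58 = 42% unerupted at 6 months with monitoring and 1 − (0.58 × 1.50) = 13% with traction. These do not measure missing T3 scores. Children unerupted at 6 months continue in care and may align later, and the text schedules no six-month questionnaire for anyone.

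**The instrument's age range.** It is described as for ages 8 to 10 and entry runs to 10.5 years, but the article does not say how much later one arm reaches T3, so no between-arm effect can be claimed.

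**Conclusion.** The point holds in a limited form. The T0 score is collected but is not a covariate in any stated analysis, and the retention rule could drop it even if it were listed. The cost is avoidable imprecision on a secondary outcome: 35% to 10% of variance against a change-score comparison as ρ rises from 0.3 to 0.8, and 9% to 64% against a post-score comparison. These figures rest on assumed correlations, equal variances and a common slope. They do not show bias or a contradiction in the plan.

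The event-driven timing of T3 and T4 is a real limit on interpretation but a matter of design. It calls for a clear statement in the report, not a different main comparison.

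**What to change.** **Main change.** In Statistical methods {20a}, state that the quality-of-life total and sub-scores at T3 and at T4 will each be analysed by a linear model with treatment group and the T0 score as a prespecified covariate, exempt from the 10% change-in-estimate rule. Report the adjusted group difference with its 95% confidence interval. This needs no new data and one added sentence. If an unseen SAP or full protocol already does this, it is enough to align the article's wording.

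**Reporting note.** State that the quality-of-life comparison applies once the tooth is aligned, that time since surgery may differ between arms, and that it does not cover the waiting period. Give the number in each arm with a T3 and a T4 score, and the time from surgery to each.

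**Optional.** Add the same questionnaire at 6 months after surgery for every randomised child, as a supportive analysis beside the pre/post-treatment comparison. The cost is one extra questionnaire per child. The text names a six-month point only for non-eruption, so the time point would have to be arranged for children whose tooth has already erupted.

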### Trial design {8}

This is a multicentre randomised clinical trial consisting of two parallel groups with equal randomisation to detect the superiority of one intervention over the other. Randomisation of the participants to one or two groups will be undertaken to ensure unrestricted equal participant allocation (1:1). This process will be undertaken centrally to ensure random allocation and concealment.

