### Methods for additional analyses (e.g. subgroup analyses) {20b}

Except for the adjusted-for-confounders analyses detailed above, no other additional analyses or subgroup analyses are planned.

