### Methods in analysis to handle protocol non-adherence and any statistical methods to handle missing data {20c}

Statistically significant RRs will be translated in a clinically relevant manner using risk differences and the number needed to treat. If multiple impacted teeth per patients are included, within-patient clustering will be taken into account with robust standard errors. If any centre effects are identified, these will be accounted for with a random term in the model.

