## Discussion

This trial was planned to commence prior to 2020. However, given the disruption caused to clinical services by the COVID-19 pandemic, a delay in commencing would appear advantageous, but challenges still remain. The recruitment of participants into this trial is currently limited to secondary care services (orthodontics, paediatrics and oral survey) which are under pressure to reduce patient treatment waiting lists and restoring clinical activity to pre-COVID levels. The participants with the index condition for this trial are deemed a high need for treatment as per the Index of Orthodontic Treatment Need (IOTN) [27] and are commonly referred from primary care to second care environments as a multi-disciplinary management is often required. On this basis, we do not anticipate difficulty in achieving the required sample size as recruitment of patients is being undertaken across nine sites. However, future rises in COVID-19 infections could impact recruitment especially if national restrictions are reactivated and staff at recruitment sites are redeployed. To manage potential recruitment issues, the inclusion of additional recruitment sites will be considered.

As encountered by other clinical trials in orthodontics, blinding of both participants and investigators at recruitment sites will not be possible. To minimise bias, the randomisation (allocation and concealment) will be undertaken centrally at a Clinical Trials Unit. Furthermore, both the investigator assessing the clinical records and the statistician will be unaware of the participant trial arm allocation.

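### The 10% change-in-estimate rule chooses covariates for the adjusted models by chance imbalance, and it is the only stated route to the tooth-position objective

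*Protocol article*

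**What the plan says.** All references are to the protocol article.

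- **Covariates.** Section {20a} lists candidates in advance: "Possible risk factors that are planned a priori to be investigated include patient age, patient sex, patient ethnicity, impacted incisor’s maturity, impacted incisor’s position". The list goes on to the number or morphology of the supernumeraries, and it breaks position down into orientation, inclination and height. The section then calls these candidates confounders and builds the adjusted models "by adding one covariate at a time in the simple model and retained if the change-in-estimate is at least 10"%. No covariate is certain to be in the model. The section does not say whether the 10% is measured on the RR or on its logarithm.
- **Centre.** Section {20c}: "If any centre effects are identified, these will be accounted for with a random term in the model". The Discussion says that "recruitment of patients is being undertaken across nine sites".
- **Unselected analyses.** Section {20a}: "The initial crude differences between the groups will be assessed with the chi-square test for the primary outcome", with t-tests for secondary outcomes, followed by crude generalised linear models giving an RR or an unstandardised coefficient.
- **Tooth position.** Section {12} names as secondary outcome (1) "the effect of initial tooth position (assessed radiographically) on the time taken for the tooth to erupt"; section {7} has the same objective. In {20a}, position appears only in the candidate list.
- **Anything else.** Section {20b}: "Except for the adjusted-for-confounders analyses detailed above, no other additional analyses or subgroup analyses are planned".

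**The concern.** Change-in-estimate is a screen for confounding in observational data. Under random allocation there is no systematic confounding to find. Adding a covariate moves the treatment estimate mainly through chance imbalance on that covariate, and the 10% is taken relative to whatever treatment effect was observed. The usual reason to adjust in a trial is to gain precision from strong predictors, and the rule does not look at that: a strong but well-balanced predictor fails, while noise can pass when the observed effect is small.

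Two things are at stake. The adjusted effect would come from a model chosen by this trial's own data, with some precision given up. And secondary objective 1 asks whether position affects time to eruption, whereas the rule asks whether position shifts the treatment effect. Position can matter greatly for eruption time and still fail the rule.

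**Working it through.** **Inputs.** From section {14}: 58% eruption in controls, RR 1.50 (0.58 × 1.50 = 0.87), 40 per group analysed, 40 × 1.15 = 46 per group recruited. From {20a}: the 10% rule. Covariate strengths are not in the documents and are assumptions here; two values are shown where possible.

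**The plan's own figure.** For 58% against 87%, two-sided 5%, 80% power, standard variants give 38 per arm (noncentral chi-square) to 41 (exact power of Fisher's test 0.803; 0.790 at 40). The stated 40 is reproduced closely and is not disputed.

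**1. A balanced predictor is discarded.** Take 40 per arm with 23/40 and 35/40 erupted, so RR = 35/23 = 1.5217. Let a binary covariate be split equally in both arms, with 23/40 and 35/40 erupted at its two levels, so its own RR is also 1.5217. A log-link Poisson model gives a treatment RR of 1.5217 both without and with the covariate. The change is 0%, so the rule drops it.

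**2. Retention on the coefficient scale (continuous outcome, residual SD 1).** With 40 per arm, a standardised covariate differs between arms by chance with SD √(2/40) = 0.2236. A covariate of correlation b with the outcome moves the treatment estimate by about b × 0.2236 × Z, where Z is standard normal. At a true effect of 0.63 SD the threshold is about 0.1 × 0.63 = 0.063.

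- b = 0.5: 0.063 / (0.5 × 0.2236) = 0.563; P(kept) = 2(1 − Φ(0.563)) = 0.57.
- b = 0.7: 0.063 / (0.7 × 0.2236) = 0.402; P(kept) = 2(1 − Φ(0.402)) = 0.69.

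Simulation of the rule agrees:

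| Covariate | Kept, true effect 0 | Kept, true effect 0.63 SD |
|---|---|---|
| Pure noise | about 40% | 6 to 7% |
| Correlation 0.5 | 88 to 90% | 55 to 57% |
| Correlation 0.7 | 94% | 68% |

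So at 0.63 SD the predictor of correlation 0.5 is dropped in about 43 to 45% of trials, and the one of correlation 0.7 in about 32%. With nine noise candidates and no effect, at least one is kept in 90% of trials.

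**3. Retention for the primary outcome (control 58%, one binary covariate with RR 1.6).**

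| Scale of the 10% | Kept at treatment RR 1.0 | Kept at treatment RR 1.5 |
|---|---|---|
| Log-RR coefficient | 73% | 43% |
| RR itself | 9% | 6% |

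On the RR scale this predictor is dropped in 91 to 94% of trials. Two analysts following {20a} could therefore fit different models to the same data.

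**4. Cost in power (continuous outcome, 0.63 SD).**

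| Correlation | Crude | 10% rule | Covariate fixed in advance |
|---|---|---|---|
| 0.5 | 0.80 | 0.87 | 0.90 |
| 0.7 | 0.79 | 0.94 | 0.97 |

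The rule loses about 3 points against a fixed covariate here. A separate linear simulation with nine candidates, four of them prognostic, gave 83% against 85%, a loss of 2.

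**5. Tooth position.** Set side by side, {12} asks for the effect of position on eruption time, {20a} admits position only as a candidate under the 10% rule, and {20b} plans nothing further. By steps 1 to 3, whether position is retained says little about its effect on eruption time.

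**The case against.** The strongest reply is that the main result is safe. Section {14} powers the trial on a chi-square test, {20a} puts that test first with a crude RR after it, and adjustment comes only as a further step. The candidate list is fixed in advance. All of this stands. A reader might infer that the primary result itself is data-chosen, or that crude and adjusted tests compete for the claim. The documents do not support that: the crude analysis is unselected and is the powered one, and no rule lets either test succeed. Nor is there a case for materially inflated type I error: with nine noise covariates the selected model rejected in about 6.3% of null trials against 5.1% crude.

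It is also fair that the near-null instability belongs to the coefficient scale; on the RR scale retention hardly varies with the effect. But there the rule discards almost everything, so it does no useful work.

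On position, a reader might infer that its effect is never estimated. That goes too far: adding covariates one at a time means fitting a model that contains position, and {20a} says these factors are to be investigated. What is missing is any commitment to report that coefficient if position fails the screen.

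The criterion for identifying a centre effect is detail that an analysis plan may supply. The conditional entry of centre is, however, stated in the article.

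Finally, section {8} says randomisation "will be undertaken to ensure unrestricted equal participant allocation (1:1"). A reader might see a flaw in allocation too. The wording is loose, since unrestricted allocation cannot guarantee equal arms, but the method is valid. Averaged over the possible splits of 92 patients, chi-square power is 89.4% against 89.5% at 46:46. That gives no ground for changing the randomisation.

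**Conclusion.** The point holds for the adjusted models and for secondary objective 1, not for the crude primary comparison. The 10% rule selects on chance imbalance relative to the observed effect, on a scale left open for the primary outcome. Its cost in power is modest, about 2 to 3 points against covariates fixed in advance. The retention and power figures rest on assumed covariate strengths, 40 per arm and mostly a continuous outcome; the direction follows from the rule itself and needs no such assumption. The mismatch between the tooth-position objective and its analysis is a matter of text and does not depend on simulation. This should be corrected, but it does not threaten the validity of the trial.

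**What to change.** - Delete the 10% rule.
- State that the crude chi-square test and RR are the primary analysis, or name one adjusted model as primary.
- In the adjusted models for all outcomes, always include a small covariate set fixed in advance (for example baseline incisor height and inclination), with centre as a random term whatever the data show.
- Always report the position coefficients, with confidence intervals, from the time-to-eruption model, so that secondary objective 1 has its own analysis.

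This is a change of wording that can be made at any time before the data are analysed; it needs no extra patients or measurements. The small downside is that the chosen covariates may turn out to be weak predictors, in which case little precision is gained.

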#### Sample size {14}

Sample size calculation was based on three previous studies [11, 12, 14], random-effects meta-analysis of which indicated that in 58% of cases (95% = 40–75%; *I*^2^ = 85%), the maxillary permanent central incisor erupts spontaneously after surgical removal of the supernumerary tooth. Assuming a moderate relative risk = 1.50 as clinically relevant, equal 1-1 distribution between the groups and aiming to find a difference using a chi-square test with *α* = 5% and *β* = 20% (power of 80%), a total of 40 patients per group would be needed. Adding an additional 15% for possible drop-outs, the aim was set at 46 patients/per group (92 in total).

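### A superiority trial names per protocol as the basis of every analysis and plans no as-randomised analysis

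*Protocol article*

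**What the plan says.** The Trial design section sets up "two parallel groups with equal randomisation to detect the superiority of one intervention over the other". The Statistical methods section for primary and secondary outcomes then fixes the analysis basis: "All analyses will be done per protocol by the statistician in a blind manner using a coded dataset". The same sentence goes on to name the software and the two-sided 0.05 level.

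Two later sections could have added an as-randomised analysis, and neither does:

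- The section on additional analyses says that, apart from the confounder-adjusted models, "no other additional analyses or subgroup analyses are planned".
- The section on non-adherence and missing data covers number needed to treat, clustering of teeth within a patient and centre effects. It says nothing on how children who deviate are analysed.

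The article does not say which deviations would remove a child from the per-protocol set.

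**The concern.** Randomisation makes the two groups comparable as allocated. A per-protocol set is formed afterwards, and if the reasons for exclusion are related to whether the tooth erupts, that comparability is lost. A superiority claim would then rest on an observational comparison, with no as-randomised result beside it.

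The design leaves room for this. Children are randomised after space creation and before surgery (Intervention description), and the primary endpoint is eruption within 6 months of surgery (Outcomes). Clinicians and families know the allocation (Who will be blinded). Deviations in that window are possible in both arms:

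- In group 1, the bonded attachment could be lost or traction interrupted.
- In group 2, a child whose tooth is slow to erupt could receive traction or a further procedure early.

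Either event plausibly goes with non-eruption. Blinding the statistician with a coded dataset does not help if the decision that a child deviated is made at the site by people who know allocation and outcome.

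**Working it through.** **The plan's own figures.** Sample size section: comparator eruption rate 58%, relative risk 1.50, so 0.58 × 1.50 = 0.87 in the other group; two-sided 5%, power 80%, 40 per group. The standard two-proportion formula gives 37 per group without continuity correction and 43 with it; the log relative risk formula gives 42. The stated 40 lies among these, and the uncorrected chi-square has power 0.84 at 40 per group. The drop-out step is 40 × 1.15 = 46. The sample size is therefore not in dispute, and 58% and 46 per group are used below.

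**Illustration of bias, exclusions in group 1 only.** Assumptions not in the article: no true difference (58% in both arms), and a share *e* of group 1 failures is excluded while nobody else is. Then:

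- expected number excluded = 46 × 0.42 × *e*
- group 1 size = 46 × (1 − 0.42*e*), rounded
- group 1 rate = 0.58 / (1 − 0.42*e*)
- apparent relative risk = 1 / (1 − 0.42*e*)

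Type I error is the sum of the binomial probabilities of all tables in which the uncorrected Pearson chi-square is significant at two-sided 0.05.

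| Share of group 1 failures excluded | Children | Group 1 size | Group 1 rate | Apparent RR | Type I error |
|---|---|---|---|---|---|
| 0% | 0 | 46 | 58.0% | 1.00 | 4.6% |
| 5% | 1.0 | 45 | 59.2% | 1.02 | 5.6% |
| 10% | 1.9 | 44 | 60.5% | 1.04 | 5.5% |
| 20% | 3.9 | 42 | 63.3% | 1.09 | 8.0% |
| 30% | 5.8 | 40 | 66.4% | 1.14 | 12.6% |
| 40% | 7.7 | 38 | 69.7% | 1.20 | 19.8% |

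The 5% and 10% rows are out of order only because the group size is rounded to whole children.

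**Other patterns of exclusion, same method.**

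- Same share of failures excluded in both arms (20%, 30%, 40%): 5.5%, 4.8%, 5.2%.
- Group 2 share half that of group 1 (group 1 at 20%, 30%, 40%): 6.0%, 7.0%, 9.6%.
- Failures excluded from group 2 only: the same error rates as in the table, by symmetry, but with the bias running against traction.
- Exclusions unrelated to outcome: no bias of this kind.

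**Power of the as-randomised analysis.** With 46 per group, power = Φ[(d√n − 1.96√(2p̄(1−p̄))) / √(p₁(1−p₁) + p₂(1−p₂))]. At 0.87 v 0.58: d = 0.29, p̄ = 0.725, and (1.967 − 1.238) / 0.597 = 1.22, so power is 0.889. Now assume that a share *s* of group 1 does not receive its allocated treatment and erupts at 58%, so that p₁ = 0.87(1 − *s*) + 0.58*s*:

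| *s* | p₁ | RR | Power |
|---|---|---|---|
| 0% | 0.870 | 1.500 | 0.889 |
| 5% | 0.856 | 1.475 | 0.847 |
| 10% | 0.841 | 1.450 | 0.798 |
| 15% | 0.827 | 1.425 | 0.743 |

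These figures take the outcome as known for all 46 per group.

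**The case against.** **The phrase may be loose.** It could mean only that the statistician will follow the protocol, since it stands among procedural details such as coding and software. On that reading it directs no exclusions. In a statistical methods section the analysis-set meaning is the more natural one, but the ambiguity is real. What stands on either reading is that the article states no as-randomised analysis.

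**The detail may be elsewhere.** A definition of the set, and the handling of missing outcomes, can properly sit in an analysis plan that is not shown. Their absence is not the point here. The article fixes the basis for all analyses, so a plan that made the as-randomised analysis primary would contradict it if the phrase carries its usual meaning.

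**Failures may not be dropped at all.** A reader might infer that the primary comparison will remove children because treatment failed. The article does not say so. Its one section on changing treatment after non-eruption (Criteria for discontinuing or modifying allocated interventions) applies once the 6 months have passed, covers both groups and is allowed by the protocol. A tooth unerupted at 6 months is simply a counted failure.

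**The bias may not favour traction.** A reader might also infer that it does, because only group 1 carries a bonded attachment before eruption. The article neither classes loss of the attachment as an excluding deviation nor gives a rate for it. Early intervention in group 2 would be a deviation tied to failure as well, and excluding those children would push the other way.

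**Conclusion.** The concern holds in a limited form. A trial planned "to detect the superiority of one intervention over the other" names an undefined per-protocol basis for all its analyses and plans no as-randomised analysis. That gives up the protection of randomisation for the primary comparison, and it should be corrected before outcomes are known.

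Outcome-related exclusion is a possibility that the design permits; the plan does not prescribe it, and its direction is open. The type I error figures, from about 5.6% to about 20%, illustrate one-sided exclusion of failures under assumed shares and are not an estimate for this trial. Under balanced exclusion of failures the error stays near 5%.

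**What to change.** Replace the sentence with wording such as: *All randomised participants will be analysed in the group to which they were allocated, for the primary and secondary outcomes, by the statistician using a coded dataset. A per-protocol analysis, with the excluding deviations defined before the data are examined, will be reported as a sensitivity analysis.* Amend the section on additional analyses to list that sensitivity analysis. The handling of children whose 6-month status is unknown can be set out in the analysis plan.

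The cost is one sentence, one extra table and some dilution of the effect if children do not receive their allocated treatment. On the assumptions above, 46 per group keeps about 80% power up to roughly 10% non-adherence in group 1, and about 74% at 15%.
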